### Missing data

Stringent attempts will be made to minimise missing data through checking of questionnaires as they are completed, and returning to participants to retrieve missing items. Participants with missing outcome data at a specific time point will be excluded from analysis at that stage. Multiple imputation will be used to estimate missing outcome scores in repeated measures analysis.

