4. Assess the costs of the specialist rehabilitation intervention, and of the ongoing care assistant support, and calculate relative cost-effectiveness, including consideration of savings from service use offsets;

5. Investigate the acceptability of the new service delivery models (specialist domiciliary rehabilitation with and without ongoing support from trained care assistants) from the perspectives of all stakeholders including commissioners, MDT members, care assistants, service managers, patients and family carers;

6. Deliver guidance for commissioners, providers and policy makers about the acceptability, clinical and cost-effectiveness of different models of specialist neurological rehabilitation.

The **hypotheses **are that:

1. A package of domiciliary multidisciplinary specialist rehabilitation will benefit:

a. People with Parkinson's in terms of maintaining mobility and independence (primary outcome for patients), and improving wellbeing and health-related quality of life,

b. Family carers in terms of reduced strain (primary outcome for carers), and improved health-related quality of life, and

c. Society through reduced use of other health and social care services, including hospitalisations and admissions to long term care.

2. The addition of four months of ongoing support from trained care assistants will help to maintain the benefits of the specialist team rehabilitation, and avoid the fading of effects that typically accompanies the withdrawal of input.

3. The intervention will be acceptable to major stakeholders, and that barriers and facilitators to wider implementation will be identified.

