### Inclusion criteria

People with Parkinson's (any stage of the disease) will be included if they: are 18 years of age or over; have a clinical diagnosis of Parkinson's disease; are living in the community (own home or minimally sheltered accommodation) with their own living areas; live in the county of Surrey (for reasons associated with the funding of the intervention); are able to read and write English in order to complete the self report questionnaires; express a commitment to participate over the duration of the study and provide written consent.

Live-in carers will be included if they: are 18 years of age, or over; are able to read and write English in order to complete the self report questionnaires; express a commitment to participate over the duration of the study and provide written consent.

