### Exclusion criteria

Exclusion criteria will be checked by the research nurse at the baseline assessment. People with Parkinson's will be excluded if they: score at the most favourable end of all outcome scales at baseline, because the trial cannot demonstrate an improvement in these patients, and, in six months, has little likelihood of demonstrating reduction in any expected decline; score less than 24 on the mini mental state examination at baseline assessment [44], to ensure those recruited can follow instructions associated with the rehabilitation intervention; are already having a multidisciplinary package of care, or have had such care in the last six months; are taking part in another rehabilitation-based research study, or have taken part in such research in the last six months.

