### Outcome measures

Participants in all groups will be assessed in their homes by a research nurse, according to the schedule used in the day hospital trial, at weeks 6 (after the rehabilitation intervention), 24 (four months after the end rehabilitation, coinciding with the end ongoing support for Group B), and 36 (for final follow up). Validated instruments which reflect the needs of participants (e.g. functional outcomes, quality of life) and service commissioners (e.g. service use), and which have been found sensitive in previous rehabilitation studies undertaken by the research team [10-13] have been selected to measure outcomes (Table 1).

**Table 1 T1:** Trial outcome measures and instruments: baseline, 6, 24 and 36 weeks

Participant	Outcome measure	Instrument
Person with Parkinson's	Parkinson's disability/general activities	Self Assessment Parkinson's Disease Disability Scale [46] (PRIMARY OUTCOME)
	
	Parkinson's specific	Parkinson's Disease Questionnaire [47]
		
		Non Motor Symptom Questionnaire [48]
	
	Mobility	Posture and gait items from the Unified Parkinson's Disease Rating Scale [49]
		
		Timed up and go [50]
	
	Falls	Self report
	
	Speech	Single speech item from the Unified Parkinson's Disease Rating Scale [49]
		
		Abridged Emerson and Enderby Screening Assessment Rating Scale [51]
		
		Frenchay Dysarthria Summary [52]
		
		Speech self report questionnaire [10-12]
	
	Pain	Visual analogue scale [53]
	
	Generic health related quality of life/QALYs	Euro Qol 5D, with utility index for calculation of quality adjusted life years (QALYs) [54]
	
	Self efficacy	Self efficacy scale [55]
	
	Health and social care utilisation	Customised proforma and patient records

Live-in carer	Carer strain	Modified caregiver strain index [56] (PRIMARY OUTCOME)
	
	General health	General health questionnaire - 12 [57]

Both	Activities of daily living	Barthel ADL index [58]
	
	Social activities	Frenchay Activities index [59]
	
	Psychological wellbeing	Hospital Anxiety and Depression Scale [60]
		
		Yale single item depression screening tool [61]
	
	Generic health related quality of life	Short form - 36 Health Survey [62]

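### The blanket exclusion of missing scores drops patients who cannot perform Timed up and go, which can bias that secondary comparison in either direction

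*Protocol article*

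**What the plan says.** - **Population.** Inclusion criteria: "People with Parkinson's (any stage of the disease) will be included if they: are 18 years of age or over". The remaining criteria cover diagnosis, community living, residence, English literacy, commitment and consent. None concerns standing or walking.
- **Exclusion on function.** The only exclusion based on the outcome scales applies at the good end, to patients who "score at the most favourable end of all outcome scales at baseline". Nothing closes the severe end.
- **Instruments.** Table 1 lists two mobility measures, collected at baseline and weeks 6, 24 and 36: the posture and gait items of the Unified Parkinson's Disease Rating Scale (UPDRS), and Timed up and go. Neither is marked as primary.
- **Analysis.** Statistical methods tests mobility on change scores, from baseline to weeks 6, 24 and 36 and also from week 6 to week 24. The test is a t test, or Mann Whitney U if its assumptions clearly fail.
- **Missing scores.** The Missing data section says: "Participants with missing outcome data at a specific time point will be excluded from analysis at that stage". It continues: "Multiple imputation will be used to estimate missing outcome scores in repeated measures analysis".
- **Principle.** The sample size section ends by stating an intention to treat analysis.

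**The concern.** Timed up and go needs a patient who can rise and walk. A patient who cannot has no time to record, and checking forms or going back to the participant cannot recover one. The empty field is itself a very poor mobility result, so the missingness depends on the outcome being measured. The exclusion rule treats this like a form that was not filled in.

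Two groups of patients are affected. Those who become unable during follow-up leave the comparison at the visit where they have done worst. Those already unable at baseline have no change from baseline at any visit. Neither loss fits well with intention to treat, or with a hypothesis about maintaining mobility. What is at stake is the direction and size of the Timed up and go contrast, and whether it describes patients at all stages.

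**Working it through.** **1. The plan's own figures.** The protocol gives no figure for Timed up and go. Its sample size concerns the disability scale and reproduces: a difference of 1.25 with SD 2.5 is 0.5 SD; a two-sided 5% t test with 80% power needs 63.8, so 64 per group. The carer calculation (0.535/1.07 = 0.5 SD) also gives 64. Inflation: 64 × 3 / 0.79 = 243.04, and 243.04 / 0.90 = 270.04, stated as 270, or 90 per group. None of this depends on Timed up and go. After 10% loss, 90 × 0.90 = 81 per group remain, which is the size used in step 4.

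**2. Does the rule reach these patients?** Any stage is eligible and no criterion requires walking. The test gives no time for someone who cannot walk, a change score needs both visits, and a missing score is excluded whatever the reason. The imputation sentence covers a repeated measures analysis, whereas Statistical methods describes tests of change scores over stated intervals. An imputed time would in any case stand for a walk the patient could not do.

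**3. Bias in the mean difference (assumed inputs).** Let the latent change have SD 1 with higher meaning worse, mean 0 in control and −d in the active group. Write λ(a) = φ(a)/Φ(a), the amount by which cutting a standard normal above a lowers its mean.

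*One threshold for both groups*, a = Φ⁻¹(1 − p), where p is the share of controls who become unable:

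observed benefit = d − λ(a) + λ(a + d).

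For d = 0.50:

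| Controls unable | Active unable | λ(a) | λ(a + d) | Observed benefit | Share of true |
|---|---|---|---|---|---|
| 2% | 0.5% | 0.049 | 0.015 | 0.47 | 93% |
| 5% | 1.6% | 0.109 | 0.041 | 0.43 | 86% |
| 10% | 3.7% | 0.195 | 0.085 | 0.39 | 78% |
| 20% | 9.0% | 0.350 | 0.178 | 0.33 | 66% |

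Simulation gives the same values. With d = 0 the two λ terms cancel and there is no bias. With a true harm of 0.25 SD, the observed harm shrinks to between 0.22 and 0.14 SD.

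*Group-specific loss of the worst patients*, d = 0.50:

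- Equal loss (5% or 10% in each group): the terms cancel and 0.50 stays 0.50.
- 10% of controls and 5% of active: 0.50 − 0.195 + 0.109 = 0.41.
- 5% of controls and 10% of active: 0.50 − 0.109 + 0.195 = 0.59. The same losses turn a true zero into an apparent benefit of 0.09.

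**4. Power, 81 per group, d = 0.50, one threshold (3,000 simulated trials each).** The complete-case t test has power of about 0.88 with almost no loss, then 0.85, 0.83, 0.78 and 0.66 at 2%, 5%, 10% and 20% of controls unable. Mann Whitney with the unable ranked worst stays between 0.86 and 0.88.

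**5. A second model, in seconds.** Assume a median time of 15 s, log SD 0.4, a relative benefit of about 10%, and inability above a fixed latent time that 5% exceed at baseline. The complete-case difference is −1.35 s against −1.74 s (1 − 1.35/1.74 = 22%, or 23% before rounding). With 1% and 10% unable at baseline it is 13% and 28% too small. This model assumes controls slow by about 16%; with 2% slowing, the shrinkage at 5% unable falls to 16%.

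**The case against.** The strongest objection is that the article never says a patient who attends but cannot do the test is coded as missing. A scoring convention for one secondary instrument may sit in the full protocol or analysis plan, which are not shown. That stands as a limit on what can be known, and silence on scoring alone would be no finding. The exclusion rule, however, is stated in the article without regard to reason, and it fits this outcome badly.

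A reader might go further than the protocol supports in three ways:

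- *That benefit is understated.* This holds only if fewer patients lose walking in the active groups. The bias is nil with equal loss and reverses if the active groups lose more. Risks and adverse events accepts that encouraging exercise could cause extra falls, so the reversed case cannot be dismissed.
- *That these patients vanish from the mobility assessment.* They do not. The posture and gait items are rated and need no completed timed walk; the Barthel index and the disability scale do not need one either.
- *That the primary outcome is affected.* The hypotheses attach the primary label to "People with Parkinson's in terms of maintaining mobility and independence (primary outcome for patients), and improving wellbeing and health-related quality of life", but Table 1 gives it to the disability scale for patients and to carer strain for carers.

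The sizes also rest on assumed rates. Participants are volunteers living in the community with a mini mental state score of at least 24, so the higher rates of inability are less certain. The model in seconds has a further weakness: its true difference includes latent times for people who cannot walk.

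**Conclusion.** The point holds for Timed up and go alone. Any-stage enrolment, a test that needs walking, change scores and a blanket exclusion rule together remove the worst outcomes on that instrument. The resulting missingness depends on the outcome, and the imputation sentence does not repair the per-visit tests.

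The direction of the bias is conditional: toward understating benefit if the intervention preserves walking, none if there is no effect and the worst patients are lost equally, and toward overstating benefit if the active groups lose more. The size cannot be fixed from the protocol. With 2% to 20% of controls becoming unable and one threshold for both groups, a true 0.50 SD appears as about 0.47 to 0.33 SD; with 5% of controls and 10% of active lost, it appears as 0.59 SD.

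This is a worthwhile, inexpensive improvement to a secondary analysis. It does not threaten the trial's primary conclusions.

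**What to change.** 1. At each visit, have the research nurse record 'unable because of mobility' separately from 'not done for other reasons'. The reason may not be recoverable later.
2. For Timed up and go, limit the exclusion rule to scores missing for other reasons.
3. Score inability. One option is to rank newly unable patients worst in the Mann Whitney test already in the plan. The other is to analyse speed (1/time) with inability set to 0.
4. State how patients unable at baseline are handled. The speed option gives them a change score. Ranking only the newly unable worst does not, so that option needs its own rule for them.
5. Report the number unable by group and visit, including baseline.

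The cost is one tick box and a sentence or two in the analysis section. The main Timed up and go result becomes a rank or speed contrast, with the difference in seconds among those able as a supplement. No change to sample size or primary analysis is needed.

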If we allow for 10% loss to follow up/non completion/missing data rates for people with Parkinson's, then 243.04/.90 = 270.03 patients are required = 90 per group. With 90 patients per group, we expect to recruit 71 carers per group. These group sizes will also ensure that the samples for patients and carers will both remain above the critical values of 64 if there were a loss of 5% of carers (and associated patients) and an independent loss of 5% of people with Parkinson's. Intention to treat analysis will be used.

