### Statistical methods

Data will be entered into an SPSS (latest version) computer data-base using the registration number to identify the participant. All paper data will be stored in a secure locked cabinet, and all computer data will be stored on a secure server.

Baseline data will be analysed to describe the characteristics of the participants and to check for significant imbalance between the three groups. All outcomes will be analysed at each follow up assessment point (six, 24 and 36 weeks), and specific *a priori *hypotheses will be tested reflecting the outcomes that we expect to identify at the different stages. In each case a two sided test will be used. It is expected that t tests will be conducted to compare groups, unless any obvious deviations from t test assumptions are found in the outcomes, in which case the non - parametric Mann Whitney U test will be used.

In order to identify short term benefits, participants in the specialist rehabilitation groups (A and B) will be compared with participants receiving information pack only (group C) at six weeks. The null hypotheses will be tested, that there are no differences between the groups, with respect to change in patient disability, mobility and psychological wellbeing, and in carer strain. These hypotheses will be tested using each participant's change score from baseline (week 0) to week 6.

In order to identify medium term benefits, comparisons will be made at 24 weeks between pairs of treatment groups (Group A vs. Group B; Group A vs. Group C; Group B vs. Group C). The null hypotheses will be tested, that there are no differences between the groups with respect to change in patient disability, mobility, falls, speech, activities of daily living, social activities, psychological wellbeing, health related quality of life and use of health and social care services, and in carer strain, social activities and health related quality of life. These hypotheses will be tested using each participant's change score from baseline (week 0) to week 24.

In order to show loss or maintenance of benefit resulting from specialist rehabilitation, Group A (no ongoing support weeks 7 and 24) will be compared with Group B (ongoing support weeks 7 to 24) using the hypotheses in the medium term analysis and each participant's change score from week 6 to week 24.

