In order to identify longer term benefits, comparisons will be made at 36 weeks between pairs of treatment groups (Group A vs. Group B; Group A vs. Group C; Group B vs. Group C). The null hypotheses will be tested, that there are no differences between the groups with respect to change in patient disability, mobility, falls, speech, activities of daily living, social activities, psychological wellbeing, health related quality of life and use of health and social care services, and in carer strain, social activities and health related quality of life. These hypotheses will be tested using each participant's change score from baseline (week 0) to week 36.

An additional exploratory analysis will be performed using each participants change score for the above outcomes between week 24 and week 36. This is the follow-up period, and this analysis will provide evidence of trends in each group, and difference between groups, after all interventions cease in week 24.

It is recognised that multiple statistical tests are being undertaken, but no adjustments will be needed for multiple testing because *a priori *hypotheses have been stipulated, and the selective reporting of significant results will be avoided. Any additional exploratory (hypothesis generating) data analyses will make allowance for multiple testing in the usual way (Bonferroni).

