## Discussion

The SPIRiTT trial is a community based MDT rehabilitation intervention for people with Parkinson's disease and their live-in carers. The intervention is delivered to people in their own homes, so that the costs and effectiveness can be compared with a similar intervention delivered to the same patient group in a day hospital setting. Findings will be compared with another community-based RCT, conducted in England recently that found no significant difference in outcomes or costs of patients receiving rehabilitation in a day hospital rather than in their own homes [66].

We anticipate several problems in the conduct of the trial and will put processes in place to avert or minimise their effect. First, retention of participants, particularly in the control group, may be difficult so we will seek to retain their interest by providing regular newsletters reporting trial progress. Patients randomised to the control group will be offered an MDT assessment and advice on completion of the trial follow up. Second, disruptions to the delivery of the MDT intervention may arise due to bad weather preventing travel, or staff sickness. We expect such interruptions will be minimal and consistent with a pragmatic approach to research on service delivery, and that cover will be available within the team for short term holiday or sickness leave. Third, lack of local NHS resources, due to financial exigencies, could impede the delivery of the intervention according to protocol to the numbers of patients and carers required by the sample size calculations, but we will liaise with local commissioners and providers to try and ensure their support. Fourth, recruiting MDT members and care assistants may be problematical, due to difficulties arranging temporary secondments from local providers, and local labour market conditions. We will address any staffing issues by advertising widely and offering favourable contracts for suitably qualified applicants. Lastly we may encounter difficulties in persuading live-in carers to take part in the research assessments, and we will seek to overcome this by explaining why their participation is important to the findings.

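### The available-case exclusion rule governs every clinical comparison, including both primary outcomes, while multiple imputation is tied to a repeated-measures analysis that the article does not describe

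*Protocol article*

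**What the plan says.** Four statements in the protocol article bear on this point.

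- **Missing data, the rule:** "Participants with missing outcome data at a specific time point will be excluded from analysis at that stage".
- **Missing data, imputation:** "Multiple imputation will be used to estimate missing outcome scores in repeated measures analysis".
- **Sample size calculations:** "Intention to treat analysis will be used". The term is not defined further.
- **Statistical methods:** "It is expected that t tests will be conducted to compare groups", with the Mann-Whitney U test as the fallback. The outcome is a change score throughout, for example "These hypotheses will be tested using each participant's change score from baseline (week 0) to week 24" and, for the longer term, "These hypotheses will be tested using each participant's change score from baseline (week 0) to week 36".

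On retention, the Discussion recognises that "retention of participants, particularly in the control group, may be difficult" and lists countermeasures: newsletters, and a team assessment for controls once follow-up is complete. Sample size calculations reports 26% loss or missing data in the earlier day-hospital trial, attributes it to transport problems and inter-current illness, and argues that home visits will reduce it. The allowance for patients is 10%. Withdrawals says that data gathered before a withdrawal will still be used.

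**The concern.** An analyst who follows the article literally drops each participant without a score at the visit in question, for both primary outcomes, and finds no listed comparison to which the imputation belongs. A second analyst, starting from the intention-to-treat sentence, might keep all 270 patients. The text does not settle which of them is right.

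Two things are at stake. The first is bias: an unadjusted test on those still observed compares like with like only if, within each arm, those lost would have changed as much as those who stayed. In a degenerative disease, with illness a stated cause of loss in the earlier trial and control-group retention a recognised difficulty, this should not be taken for granted. The second is information: a participant's week 6 and week 24 scores say a good deal about the missing week 36 score, and the rule makes no use of them there.

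**Working it through.** **Step 1. Which analyses does each missing-data rule reach?** The comparisons in Statistical methods are:

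- weeks 0 to 6: A and B against C
- weeks 0 to 24: the three pairs of groups
- weeks 6 to 24: A against B
- weeks 0 to 36: the three pairs of groups
- weeks 24 to 36, exploratory: "An additional exploratory analysis will be performed using each participants change score for the above outcomes between week 24 and week 36"

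Each uses a difference between two visits, to be compared by t test or Mann-Whitney test. Some use two follow-up visits, but none is a longitudinal model. The only model named in the article is an analysis of covariance on baseline, in Economic evaluation, and it is not described as a repeated-measures analysis. The exclusion rule therefore reaches every listed clinical comparison, and the imputation sentence reaches none that is described.

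**Step 2. Whose data are used where?**

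- Lost before week 6: in no outcome comparison.
- Lost between weeks 6 and 24: in the week 6 comparison only.
- Lost between weeks 24 and 36: in the comparisons up to week 24, but absent from week 36 although two follow-up scores exist.

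**Step 3. The plan's own numbers.** Inputs from Sample size calculations: difference 1.25 and SD 2.5 for patients, 0.535 and 1.07 for carers (0.5 SD in each case), two-sided 5%, 80% power.

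- The two-sample t-test calculation gives 63.77, so 64 per group, as stated.
- 64 × 3 / 0.79 = 243.04, and 243.04 / 0.90 = 270.04, so 90 per group.
- 90 × 0.79 = 71.1 carers per group.

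The stated sizes reproduce. Under the exclusion rule (t-test power at 0.5 SD):

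| Loss | Patients per group | Power | Carers per group | Power |
|---|---|---|---|---|
| 10% | 90 × 0.90 = 81.0 | 88.5% | 71.1 × 0.90 = 64.0 | 80.1% |
| 26% | 90 × 0.74 = 66.6 | 81.7% | 71.1 × 0.74 = 52.6 | 71.9% |

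At the planned 10% loss, about 27 of 270 patients are excluded and power holds for both outcomes. Precision is budgeted for; bias is not.

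**Step 4. Size of a possible bias.** Within an arm, the mean of all randomised is (1 − p) × (mean of observed) + p × (mean of lost), so the observed mean is off by p × gap, where p is the proportion lost and the gap is observed minus lost. With the same gap in both arms:

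bias in the contrast = (difference in p) × gap

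Assumptions, none given in the document: loss differs by 10 percentage points between arms; the gap in *change* is 0.25 to 1 SD; the planning SD of 2.5 stands for the SD of change.

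| Gap in change | Bias, disability points | Share of 1.25 |
|---|---|---|
| 0.25 SD | 0.10 × 0.25 × 2.5 = 0.06 | 5% |
| 0.5 SD | 0.10 × 0.5 × 2.5 = 0.125 | 10% |
| 1 SD | 0.10 × 1 × 2.5 = 0.25 | 20% |

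For carer strain, the same assumptions give 0.10 × 0.25 × 1.07 = 0.03 to 0.10 × 1 × 1.07 = 0.11 points, again 5% to 20% of the 0.535 target.

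**Direction.** If the extra losses are controls who were doing badly, the remaining controls look better than the full control group, and benefit in A against C and B against C is understated.

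**The case against.** The case for leaving the plan alone has real substance.

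- **Intention to treat.** A reader might infer that the exclusion rule flatly contradicts it. The document does not support that. The term is undefined, and analysing whoever is observed in the group to which they were allocated meets a common, looser reading. A likelihood model fitted to everyone with any follow-up would also leave out some randomised participants.
- **The repeated-measures analysis.** A reader might infer that no such analysis exists and that imputation can affect no result. That cannot be known from a condensed article whose full protocol and analysis plan are not shown. What can be said is that the article neither describes the analysis nor connects it to the comparisons it lists.
- **Uneven loss.** A reader might infer that the plan expects heavier loss among controls, or set 26% in group C against 10% in A or B, which with a 1 SD gap would give 0.16 × 2.5 = 0.40 points, or 32% of target. The Discussion recognises a risk and gives mitigations; it forecasts no difference. The 26% is an overall rate from a day-hospital trial, not a control-arm rate, and the article argues that it will fall.
- **Level against change.** Losing participants with more severe disease does not in itself bias a change score. The bias needs a difference in change between lost and observed participants.
- **Use of interim data.** Scores from those who later drop out are not discarded altogether; they enter the earlier comparisons, consistent with Withdrawals.

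These points limit the claim but do not remove it. The exclusion rule is stated, it applies to both primary outcomes, and an unseen analysis plan would still have to reconcile it with the other two statements.

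**Conclusion.** The point holds in a limited form. As written, available-case testing governs all listed comparisons of both primary outcomes, the promised imputation is attached to none of them, and the week 6 and 24 scores of later drop-outs do not inform the later contrasts. The fit with the intention-to-treat statement is poor rather than contradictory.

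The illustrative bias is 5% to 20% of the target difference. It rests on an assumed 10-point difference in loss and an assumed gap in change of 0.25 to 1 SD. With equal loss and equal gaps in the arms it would be zero. Its likeliest harmful form, losing controls who are doing badly, would hide benefit rather than create it. The matter should be settled before the data are analysed, because it affects every contrast on the primary outcomes and costs little to resolve.

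**What to change.** For the two primary outcomes, replace the exclusion rule with one of the following, and say which applies.

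1. **One likelihood-based repeated-measures model per outcome:** weeks 6, 24 and 36, group-by-visit terms and baseline score, including all randomised participants with any follow-up. The planned contrasts, including A and B together against C at week 6 and A against B over weeks 6 to 24, are read from it.
2. **The multiple imputation already promised,** using baseline and interim scores, applied to the stated time-point comparisons.

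Both assume that loss is explained by the data observed or modelled. Therefore keep the available-case analysis as a sensitivity analysis, and add a delta analysis in which the unobserved outcomes are made worse by an amount that may differ between arms. State in one sentence what intention to treat means here and which participants are in the primary analysis set.

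The cost is a change of wording and modest extra analysis. No new data are needed, and the sample size stays as it is.
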